### **2.6 Initial Results from Protocol 1796 "Fludarabine Lymphodepletion in Adoptive T Cell Therapy"**

Four patients have been treated on Protocol 1796 on the original protocol which included the administration of fludarabine as a lymphodepleting agent before the second T cell infusion but no inclusion of IL-2 with either the 1st or 2nd infusion. As of June, 2004, analysis of the data after treating the first 4 patients on this study has demonstrated that:

1. there are no safety concerns (i.e., no serious adverse events)
2. in vivo persistence was prolonged slightly from median of 7 to 23 days

This increase is less than expected given the anticipation that prior lymphodepletion resulting in increased serum IL-7 and IL-15 levels would result in survival for several weeks and even in vivo expansion which was not observed in the clinical trial. In fact, the increase is only slightly increased compared to a 2 week course of low-dose IL-2 (median survival of 16.9 days). Published studies performed in murine models demonstrate that even with prior depletion (e.g. with cytoxan), CD8 T cell persistence may not be prolonged unless IL-2 is also given. In this case, the use of fludarabine also ablated any potential CD4 help from the peripheral blood and, alone, did not appear to be sufficient to provide prolonged in vivo persistence. Based on these observations and previously published studies using other lymphodepleting agents in combination with IL-2, low-dose IL-2 (at a dose previously shown to be safe and effective in prolonging T cell survival in vivo) will be incorporated into the design of the study. In this study, a 14-day course of low-dose IL-2 following both the first and second T cell infusions will be administered. Since fludarabine lymphodepletion precedes only the second T cell infusion, any differences in T cell survival can be attributed to lymphodepletion alone.

Protocol 1796.00

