### **2.3 Adoptive T Cell Therapy for CMV disease using CMV-specific CD8+ CTL clones.**

The safety of adoptively transferring antigen-specific CTL clones in humans and the in vivo persistence of these clones have been examined in bone marrow transplant patients who received CMV-specific CTL clones. Studies in our Program in Immunology at the Fred Hutchinson have demonstrated that the reconstitution of endogenous CMV-specific T cell responses following allogeneic BMT correlates with protection from severe CMV disease(33, 34). CD8+ CMV-specific CTL clones were generated from CMV seropositive HLA-matched sibling donors, expanded and infused into sibling BMT recipients at risk of developing CMV disease. Fourteen patients have been treated with four weekly escalating doses of these CMV-specific CTL clones to a maximum T cell dose of  $10^9/m^2$  without any attendant toxicity. Peripheral blood was harvested from patients immediately prior to, and 2 days following each infusion and 1, 2, 4, 8 and 12 weeks after completing the infusions. The recoverable CMV-specific CTL activity increased after each successive infusion of CTL clones, and persisted at least 12 weeks after the last infusion as assessed by PCR and sequencing of the TCR genes expressed in the transferred and recovered CMV-specific CTL. No patients developed CMV viremia or disease(35). These results demonstrate that CMV-specific CD8+ CTL clones can be adoptively transferred safely to BMT recipients and can persist in vivo as functional effector cells that may provide protection from CMV disease.

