### **2.4 Adoptive T Cell Therapy for Metastatic Melanoma Using Antigen-specific T Cells**

#### **2.4.1 Adoptive T Cell Therapy – CD8+ T Cell Clones**

We recently completed a Phase I study to evaluate the safety, in vivo persistence and efficacy of adoptively transferred CD8+ T cell clones targeting the

tumor-associated antigens, MART1/MelanA and gp100 for the treatment of patients with metastatic melanoma (27). Four infusions of autologous T cell clones were administered, the first without IL-2 and subsequent infusions with low-dose IL-2 for 14 days. Forty-three infusions of MART1/MelanA-specific or gp100-specific CD8+ T cell clones were administered to 10 patients. No serious toxicity was observed. We demonstrated that the adoptively transferred T cell clones persisted in vivo in response to low-dose IL-2, preferentially localized to tumor sites and mediated an antigen-specific immune response characterized by the elimination of antigen-positive tumor cells, regression of individual metastases and minor, mixed or stable responses in 8 of 10 patients with refractory, metastatic disease for up to 21 months (27).

In the absence of co-administered IL-2, the median in vivo survival of T cells in this study was about 7 days. When T cell infusions were given with low dose IL-2 (250,000 U/m^2 s.c. twice daily) for 14 days, median T cell survival was extended to > 16 days. Attempts to enhance T cell survival beyond this period by extending IL-2 administration beyond 2 weeks will likely not be feasible due to the induction of counterregulatory mechanisms following prolonged IL-2 administration (36-38). Indeed, in this study, T cell survival began to decline by day 10, before the 14-day course of IL-2 was completed.

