Rosenberg and colleagues recently reported on the use of adoptively transferred autologous CD8+ T cell clones in patients with melanoma and showed that transferred T cells failed to persist (even after nonmyeloablative conditioning) and produced no clinical effect (39, 40) in contrast to our own results demonstrating sustained in vivo persistence and evidence of anti-tumor immunity. This discrepancy underlines the hypothesis that the manner in which effector cells are generated in vitro may be critical for their in vivo function. In the studies performed by Rosenberg's group at the NIH, T cells specific for the gp100-derived G209 epitope were isolated from patients previously immunized with a modified G209 peptide (G209M) and had failed therapy. Unfractionated peripheral blood mononuclear cells from these patients were stimulated in vitro by the addition of G209M peptide followed by high doses of IL-2 (1000 U/ml). Clones that were isolated were expanded and infused into autologous patients (who had previously failed G209M vaccination) together with high doses of IL-2 (72,000 to 720,000 U/kg three times daily) (39, 40).

By comparison, in our studies, gp100 or MART-1 specific T cells were isolated from non-vaccinated patients by cyclical antigen stimulation using autologous peptide-pulsed dendritic cells in the presence of low-doses of IL-2 (25-50 U/ml). As a consequence, the T cells that were generated expressed the high affinity IL-2 receptor upon antigen stimulation and continued to respond to low-dose IL-2 in vivo (250,000 U/m^2 twice daily - a total IL-2 dose more than 15 times lower than the lowest dose used in the NIH studies).

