#### **2.4.6. Use of Interleukin-2 in Adoptive T Cell Therapy**

Analysis of T cell persistence following 22 infusions of CD8+ T cell clones without IL-2 demonstrated a pattern of T cell survival characterized by an average increase in T cell frequency on Day 1, from  $< 1/20,000$  to  $1/480$  PBMCs or  $> 1\%$  of all CD8+ T cells, followed by a steady rapid decline to  $1/1500$  by Day 7 and  $< 1/20,000$  by Day 14. The median survival of CD8+ T cells given without IL-2 was  $6.56 \pm 0.82$  days. To extend the period of in vivo persistence, the study was modified to include four unmodified T cell infusions three weeks apart, the 2nd, 3rd and 4th infusions being accompanied by a 14-day course of low-dose IL-2 following each infusion (at doses of 0.25, 0.50 and 1.0 MU/  $m^2$  s.c. twice daily). These doses are 50- fold less than the high doses of IL-2 administered for the treatment of melanoma, do not mediate the toxicity associated with high-dose infusions, and by itself, has no anti-melanoma effect. Analysis of T cell persistence from 12 infusions of CD8+ T cell clones given with low-dose IL-2 demonstrated a pattern of T cell survival characterized by an increase in frequency to  $1/490$  PBMCs or  $> 1\%$  CD8+ cells in the peripheral blood on Day 1 that was sustained at an average of  $1/890$  PBMCs until Day 14 at which time, IL-2 was discontinued and T cell frequency fell to  $< 1/5700$  by Day 21. The average median survival of CD8+ T cells following an infusion of T cells with IL-2 was  $16.78 \pm 1.6$  days which was significantly longer than that observed in infusions administered to the same patient without IL-2.

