## Protocol 1796.00

skewed reconstitution of the immune system is required for anti-tumor effect nor that such a profound level of immunodepletion which was accompanied by serious toxicities, is necessary (or essential), given that a less severe relative lymphopenia can also provide homeostatic proliferative signals to T cells. Fludarabine at 25 mg/m^2 for 3-5 days is known to induce Grade 2-3 lymphopenia (a 30-50% decrease in lymphocyte counts) an effect that is sustained for approximately 4-6 weeks. While some risk associated with lymphopenia is occasionally observed in patients receiving multiple cycles of fludarabine therapy, the degree of immunocompromise is not nearly as severe as the cyclophosphamide/fludarabine conditioning.

This trial will also further delineate the requirements for successful immunotherapy through the adoptive transfer of a uniform population of antigen-specific CD8+ T cell clones so that the reasons for success or failure can be more clearly defined. T cells will first be given in the absence of a conditioning regimen, and then, following a 5 day course of fludarabine. Inpatient analysis of T cell persistence in vivo between the two infusions can be directly compared and the contribution of fludarabine-induced lymphopenia to extending in vivo survival of adoptively transferred T cells evaluated.

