### 4. STUDY DESIGN

This will be a single center, phase I, open-label, nonrandomized study in 12 individuals with metastatic melanoma (Stage IV disease). Antigen-specific T cells targeting one of the A2 or A3-restricted epitopes of the melanoma-associated antigens listed in Table 1 (Appendix A ) will be generated in vitro.

Patients will receive T cell infusions according to the following schedule:

[figure not shown]

Protocol 1796.00

Antigen-specific CD8+ T cell clones will be administered at a dose of  $10^{10}$  cells/m^2 for both Infusions #1 and #2. The median survival of transferred antigen-specific CTL clones in the presence of low-dose IL-2 (250,000 U/m^2) is approximately 17 days. By the end of 21 days, the frequency of transferred CTL is < 0.1% of the total CD8+ population. Fludarabine 25 mg / m^2 will be administered intravenously daily for 5 days prior to the second infusion of antigen-specific CD8+ CTL clones which will also be administered in the presence of low-dose IL-2. Four weeks after the second infusion, patients will be re-evaluated clinically and radiographic to determine the response to therapy. Serial blood draws during this time will allow us to determine if fludarabine lymphodepletion contributed to a prolongation of the median T cell survival beyond the expected 17 days seen with low-dose IL-2 alone.

If serious toxicity related to the T cell infusions is observed following infusion of CTL clones, , a regimen of corticosteroids will be given, and no further T cell infusions will be administered to the patient.

Subjects will be carefully monitored at regular intervals for a total of approximately 9 months following the last infusion. Evaluations after this time will be carried out by the referring physician who will be asked to notify us of the patient's progress. Peripheral blood from the patient will also be drawn. Patients receiving T cells will have up to approximately 4 tablespoons of blood drawn immediately prior to each infusion, 24 hours after each infusion, and then at specified intervals for 4 weeks from the last infusion (Appendix D). Samples will be used to evaluate the duration of in vivo persistence, function and trafficking of infused T cell clones. As a secondary objective, the residual measurable disease in these patients will also be followed to assess the therapeutic efficacy, if any, of these infusions. The estimated time to completion of the study is 24 months.

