All clones derived from a given study patient are labeled with the patient's initials followed by the name of the peptide for which they are specific and a number designating that specific clone. Data on cell growth and characteristics for each clone are separately recorded and these records retained. Each recipient has a separate laboratory record book for records on growth and characteristics of the T cell clones derived and grown from that individual. All records with the results of testing performed on the T cell clones are entered into the record book.

When the GMP cell sorting facility becomes available (expected date: July 2003), the following approach may be adopted for the generation of T cell clones.

A dendritic cell-enriched population of adherent PBMCs are harvested following 7-day incubation with GM-CSF and IL-4. They are pulsed with the peptide of interest and co-cultivated CD4 depleted responder T cells in 6-well plates. IL-2 (10 U/mL) is added the following day. After 7 days in culture, the cultures are harvested, washed and re-suspended in staining solution (1% human serum in PBS) containing 50  $\mu$ g/mL of PE-conjugated specific peptide-tetramer and anti-CD8 FITC antibody (Caltag) at a cell concentration of 10^7 cells/mL. After one hour at 4°C, the cells are washed and re-suspended in staining solution for flow cytometry analysis and cell sorting. CD8+ tetramer+ cells are analyzed and sorted under GMP conditions using the high-speed cell sorter at the University of Washington Clinical Research Center facility. They are directly cloned into 96-well plates containing irradiated feeder cells (5x10^4 PBL/well and 10^4 LCL/well) with 30 ng/mL of a CD3 and IL-2 (50 U/mL). Wells positive for clonal growth are selected 10 to 14 days after plating and screened in a microcytotoxicity assay to identify those clones with cytolytic activity for antigen+tumor targets. The use of tetramers is expected to decrease the time from patient enrollment (leukapheresis) to T cell infusion from 2 1/2 months to 6 weeks.

Protocol 1796.00

Table 1. Candidate Target Antigens, HLA restriction and Epitope sequence

| Antigen                  | HLA       | A.A.    | Peptide Sequence |
|--------------------------|-----------|---------|------------------|
| TYROSINASE | A2 | 368-377 | YMDGTMSQV        |
| GP100      | A2 | 154-162 | KTWGQYWQV        |

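### The fixed infusion order means the paired test compares second with first infusion, so Section 2.6 cannot credit any difference to lymphodepletion alone

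*Protocol*

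**What the plan says.** Section 2.5 fixes the order of the two conditions: "T cells will first be given in the absence of a conditioning regimen, and then, following a 5 day course of fludarabine". Appendix D puts Infusion #1 on Day 0, fludarabine on Days 21 to 25 and Infusion #2 on Day 28. Section 4 describes a "single center, phase I, open-label, nonrandomized study in 12 individuals", with no group that receives a second infusion without fludarabine.

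Section 2.6 adds a 14-day IL-2 course after both infusions and concludes that "any differences in T cell survival can be attributed to lymphodepletion alone".

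Persistence without and with fludarabine is primary objective 3.1.2. Section 12.1 calls the effect of lymphodepletion on T cell survival the primary goal, sizes the trial on it, and tests it with a one-sample t-test on within-patient differences. The only order-related threat it discusses is cells left over from Infusion #1.

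**The concern.** Giving IL-2 after both infusions balances IL-2 given at the same time as the cells. It does not balance what came before. Only Infusion #2 follows an earlier T cell infusion and an earlier IL-2 course, and it is given four weeks further into metastatic disease on Appendix D's calendar. No section requires a patient's two infusions to come from the same clone, expansion or process.

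Condition and order coincide completely, so the t-test is valid for second versus first infusion but not, by itself, for with versus without fludarabine. Any order, prior-exposure, time or product effect enters the conclusion on a primary objective and would be reported as an effect of lymphodepletion. The sign is unknown: such an effect could produce an apparent benefit or hide a real one. The point stands even if no Infusion #1 cells remain at Infusion #2.

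**Working it through.** **What the paired difference estimates.** For each patient, let D be survival after Infusion #2 minus survival after Infusion #1. Then

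E(D) = F + O,

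where F is the fludarabine effect and O is the sum of all other differences between second and first infusion. With one sequence and no unconditioned second infusion, the data give only F + O. Attribution to lymphodepletion alone requires O = 0, and nothing in the protocol establishes that.

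**Inputs.** From Section 12.1: n = 12, target difference 4 days, SD 2 days, two-sided .05, one-sample t-test, stated power about 99%. The section does not say whether the SD belongs to the paired difference or to each infusion, so both readings are used:
- SD of the difference = 2.
- SD 2 per infusion, uncorrelated: SD of the difference = 2 × √2 = 2.83.

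**Formula.** Noncentrality = difference / (SD/√n), df = 11, critical t = 2.201, rejection probability from the noncentral t distribution.

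**The protocol's own figure.**
- SD 2: noncentrality 4/(2/√12) = 6.93, power above 99.9%.
- SD 2.83: noncentrality 4/(2.83/√12) = 4.90, power 99.3%.

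Both agree with the stated figure.

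**Illustration with F = 0.** The size of O is an assumption, because the protocol gives none. A third SD is added for sensitivity. Section 2.4.6 reports 16.78 ± 1.6 days over 12 IL-2-supported infusions. If 1.6 is a standard error, the SD is 1.6 × √12 = 5.54, taken here as the SD of the difference.

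| Assumed O | SD 2 | SD 2.83 | SD 5.54 |
|---|---|---|---|
| 1 day | .35 | .20 | .09 |
| 2 days | .88 | .61 | .21 |
| 3 days | .997 | .92 | .40 |

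For O = 2 the noncentralities are 2/(2/√12) = 3.46, 2/(2.83/√12) = 2.45 and 2/(5.54/√12) = 1.25. With O = 0 every column returns .05. Simulation of 400,000 trials gave .883 and .607 for O = 2 with SD 2 and 2.83.

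**Further sensitivity for O = 2.**
- If the four patients already treated without IL-2 (Section 2.6) count toward the 12, then 12 − 4 = 8 have the current design, and the .61 to .88 range becomes .41 to .68.
- If 5.54 is a per-infusion SD with no correlation, the SD of the difference is 5.54 × √2 = 7.84 and the probability is .13.

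**The masking direction.** If F = 4 and O = −2, the expected difference is 4 − 2 = 2 days. The chance of significance falls from about 99% to the same 61% to 88% under the protocol's SD, and the effect is estimated at half its true size.

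**The case against.** The strongest defence is that the sequence is close to forced. Section 2.5 says lymphopenia after fludarabine lasts about four to six weeks, so reversing the order would carry fludarabine into the comparator. This is a small, openly nonrandomized phase I study, Objective 3.1.2 speaks only of persistence without and with fludarabine, and the disputed sentence sits in a background section. All of that stands as a defence of the design. It does not defend the word alone, since the sentence is the protocol's stated reason for reading the paired comparison causally.

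A reader might also infer from the protocol that an order or product effect has been shown. It has not:

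- **CMV series, Section 2.3** ("The recoverable CMV-specific CTL activity increased after each successive infusion of CTL clones"). These were transplant recipients given weekly escalating doses of cells that persisted for at least 12 weeks. Escalation and accumulation would explain the rise, so it does not show that a second infusion at an equal dose survives longer.
- **IL-2 counter-regulation, Section 2.4.1** ("induction of counterregulatory mechanisms following prolonged IL-2 administration"). The remark concerns extending IL-2 past two weeks. Each course here is 14 days and, on Appendix D's calendar, the first ends about two weeks before Infusion #2. (Section 12.1 gives a two-week gap between infusions; the two need reconciling.) Carry-over is conceivable but not documented, and it would be expected to shorten Infusion #2 survival.
- **Product, Section 2.4.1 and Appendix A** ("the manner in which effector cells are generated in vitro may be critical for their in vivo function"; "the following approach may be adopted for the generation of T cell clones"). The first contrasts two institutions' culture systems. The second is a process option expected from July 2003, which would mostly differ between patients, and pairing removes that. Section 2.5 calls the product uniform. Differences between one patient's two products are permitted, not reported.

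Finally, the first four patients moved from a median of 7 to 23 days (Section 2.6), beside which an order effect of 1 to 3 days is small. That comparison had the same fixed order, so it cannot rule out a larger one.

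**Conclusion.** The attribution sentence in Section 2.6 is wrong as written. The planned analysis yields a before-after difference in which fludarabine is inseparable from infusion order, prior T cell and IL-2 exposure, disease progression and any product difference. This follows from the design and needs no numerical assumption.

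The size is unknown. The 61% to 88% figure is conditional on an assumed 2-day order effect, no fludarabine effect, 12 patients and the protocol's 2-day SD. It is 41% to 68% with 8 patients and about 13% to 21% with the larger SDs. A reader might take it as the trial's actual false-positive rate; the documents do not support that, because they give no order effect of any size or sign.

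Nor is this a case for a different sequence. The point is about what the result may be said to show on a primary objective.

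**What to change.** 1. In Section 2.6, replace the attribution sentence with wording to this effect: the within-patient difference reflects fludarabine conditioning together with infusion order and prior exposure, and is a before-after comparison. Interpret the test in Section 12.1 in the same terms.
2. Where feasible, state in Section 7.2 and Appendix A that a patient's two infusions use the same clone(s) and the same manufacturing process, and record any departure. This removes one of the alternative explanations; the others remain.
3. Do not use the earlier Phase I infusions as an order control. In Section 2.4.6 IL-2 support was added with "the 2nd, 3rd and 4th infusions being accompanied by a 14-day course of low-dose IL-2 following each infusion", at 0.25, 0.50 and 1.0 MU/m² twice daily. The IL-2 dose thus appears to rise with infusion number, and change between those infusions would mix order with dose.

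The cost is a change of wording, a product-matching statement and a record of departures. The downside is a weaker attribution claim. A causal claim would need a concurrent or randomized comparison, which this correction does not ask for.

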### 3. OBJECTIVES

#### 3.1 PRIMARY OBJECTIVES

**3.1.1** Assess the safety and toxicity of cellular adoptive immunotherapy in melanoma patients using autologous CD8+ antigen-specific T cell clones following fludarabine conditioning

**3.1.2** Determine the duration of in vivo persistence of adoptively transferred CD8+ antigen-specific CTL clones without and with prior fludarabine-mediated lymphodepletion.

